## SERIOUS ADVERSE EVENTS

All serious adverse events (SAEs) will be reported to the Programme Manager at [[contact]](mailto:[contact]) ([contact]) and Sponsor - University of Southampton within 24 hours of the local site becoming aware of the event. We will use the Southampton CTU's SAE Non-CTIMP Form, which asks for the nature of the event, date of onset, severity, corrective therapies given, outcome, causality (i.e. unrelated, unlikely, possible, probably, definitely) and expectedness.

The Chief Investigator will assign the causality and expectedness of the event and the term should be in accordance with the latest version of MedDRA and grades given in accordance with the NCI CTCAE v4.03. Additional information will be provided as soon as possible if the event has not resolved at the time of reporting.

## Definitions

**Adverse Event (AE):** any untoward medical occurrence in a participant or clinical study participant which does not necessarily have a causal relationship with study treatment or participation.

An AE can therefore be any unfavourable and unintended sign (including an abnormal laboratory finding), symptom, or disease temporally associated with the study treatment or participation (regardless of causality assessments).

**Serious Adverse Event (SAE)** is any untoward medical occurrence or effect that:

- **Results in death**
- **Is life-threatening** – refers to an event in which the participant was at risk of death at the time of the event; it does not refer to an event which hypothetically might have caused death if it were more severe
- **Requires hospitalisation, or prolongation of existing hospitalisation**
- **Results in persistent or significant disability or incapacity**
- Other important medical events\*\*\*.

\*‘life-threatening’ in the definition of ‘serious’ refers to an event in which the patient was at risk of death at the time of the event; it does not refer to an event which hypothetically might have caused death if it were more severe.

\*\*Hospitalisation is defined as an inpatient admission, regardless of length of stay, even if the hospitalisation is a precautionary measure for continued observation. Hospitalisations for a pre-existing condition, including elective procedures that have not worsened, do not constitute an SAE.

\*\*\*Other important medical events May also be considered serious if they jeopardise the participant or require an intervention to prevent one of the above consequences.

**Note:** It is the responsibility of the PI or delegate to grade an event as ‘not serious’ (AE) or ‘serious’ (SAE).

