### 6.4.1 Expected Adverse Events:

|                                           |                                                                                                                                                                                                           |
|-------------------------------------------|-----------------------------------------------------------------------------------------------------------------------------------------------------------------------------------------------------------|
| Mild antidepressant withdrawal symptoms   | Likely to occur in around half of patients reducing and stopping their antidepressants. If mild enough to be tolerated by patient, and short-lived (up to two weeks), these do not need reporting as AEs. |
| Moderate to severe withdrawal symptoms    | If severe or prolonged withdrawal symptoms occur, requiring restarting of antidepressant, please report as related and expected AE.                                                                       |
| Relapse of depression or anxiety disorder | May occur in 10-20% of patients over the one year follow-up, requiring restarting of antidepressant. Please report as related and expected AE.                                                            |

The nature or severity of should be considered when making the assessment of expectedness. If these factors are not consistent with the current information available then the AE should be recorded as 'unexpected'.

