## Inclusion criteria

Our aim is to include patients who are taking long-term antidepressant treatment, which is not indicated according to the NICE depression guideline (NICE, 2009). We will therefore include all consenting:

- patients on treatment for more than 1 year for a first episode, and
- patients treated for more than 2 years for a recurrent episode, who are:
- no longer depressed or judged to be at significant risk of relapse

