#### **4.7 Safety reporting**

A listing of serious adverse events (SAEs) will be provided for all related/unrelated SAEs. If required, a summary table will also be presented.

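### A misplaced qualifier in the SAE definition allows an admission for relapse to be graded as an AE, which would keep it out of the only planned safety listing

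*Combined protocol and SAP*

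**What the plan says.** The protocol's Definitions (under Serious Adverse Events) make hospitalisation a seriousness criterion and define it broadly: "Hospitalisation is defined as an inpatient admission, regardless of length of stay, even if the hospitalisation is a precautionary measure for continued observation". The next sentence takes some admissions out again: "Hospitalisations for a pre-existing condition, including elective procedures that have not worsened, do not constitute an SAE". A further route to seriousness is left open for other important medical events, which "May also be considered serious if they jeopardise the participant or require an intervention to prevent one of the above consequences". On who decides, the section notes: "It is the responsibility of the PI or delegate to grade an event as" serious or not serious.

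Section 6.4.1 lists three expected events: mild withdrawal symptoms, moderate to severe withdrawal symptoms, and relapse of depression or anxiety. For relapse it says: "May occur in 10-20% of patients over the one year follow-up, requiring restarting of antidepressant. Please report as related and expected AE". Severe or prolonged withdrawal that leads to restarting treatment is handled the same way. The Causality section uses the protocol's list of expected events to decide whether a related SAE is expected or unexpected.

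Under Inclusion criteria, participants are "patients on treatment for more than 1 year for a first episode, and" those treated for more than two years for a recurrent episode, who must also be "no longer depressed or judged to be at significant risk of relapse".

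SAP 4.7 plans one safety output: "A listing of serious adverse events (SAEs) will be provided for all related/unrelated SAEs", with a summary table only if required.

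**The concern.** The trial asks whether antidepressant use can be reduced without depression getting worse. An inpatient admission for relapse during or after tapering is among the safety events that bear most directly on that claim. The exclusion sentence lets a grader treat such an admission as one for a pre-existing condition, and the only section that names relapse tells the site to report it as an AE.

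The grading decides where the event goes. SAEs must reach the Programme Manager and sponsor within 24 hours and are reported to the IDMC. For other adverse events, the section on participant safety leaves the Chief Investigator or a Principal Investigator to decide whether the sponsor, ethics committee, steering committee or IDMC is told. In the SAP, an event graded as non-serious is neither listed nor tabulated.

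Graders who read the sentence differently would also produce SAE counts that are not comparable. The rule for discrepant views, which takes the worst case, covers causality only, so nothing settles a disagreement about seriousness. The intervention is meant to increase tapering relative to a control arm in which 7% are assumed to discontinue, so any under-recording need not be equal between arms.

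**Working it through.** The point concerns wording. No stated sample size, power or alpha depends on it, so the check is to set the sections side by side and then look at scale.

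**1. The exclusion sentence**
- Literal reading: the words about not having worsened follow elective procedures and qualify them. The main clause, on admissions for a pre-existing condition, has no qualifier. Depression is pre-existing for every participant, so an admission for relapse is excluded.
- Likely intended reading: a procedure cannot worsen but a condition can, so the qualifier belongs to the condition. Participants must be no longer depressed at entry, so relapse is a worsening and the admission remains an SAE.

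The two readings give opposite gradings for the same event.

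**2. Whether other sections settle it**
- Section 6.4.1 directs relapse and severe withdrawal to AE reporting and gives no instruction for a case that meets a seriousness criterion. Its closing remark on nature and severity concerns expectedness, not seriousness.
- The Causality section classes SAEs as expected by reference to the protocol's list. The list given is 6.4.1, which contains only withdrawal and relapse, so that section presupposes that these events can be SAEs. This favours the intended reading but does not state it.
- The important-medical-event route is permissive, and grading rests with the PI or delegate.

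No section says how an admission for relapse is to be graded.

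**3. Where an admission graded as an AE would show up**
- SAP 4.7: no, because it lists SAEs only.
- SAP secondary endpoints (1.4.2): no, because neither relapse nor admission is one.
- GP-record extraction: yes, but under Costs, not as a safety output.
- PHQ-9 at 6 months: only indirectly. The primary analysis is of complete cases, so a patient who is admitted and misses that assessment is not in it.

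**4. Scale (illustrative)**
Inputs: N = 360 (SAP 2.2) and relapse in 10-20% over one year (section 6.4.1). The proportion h of relapses that lead to admission is not in the documents and is assumed here at 1% to 10%.

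Relapses = N × rate: 360 × 0.10 = 36 and 360 × 0.20 = 72.

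Expected admissions = relapses × h. Chance of at least one = 1 − (1 − rate × h)^360.

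| Assumed h | Expected admissions | Chance of at least one |
|---|---|---|
| 1% | 0.4 to 0.7 | 30% to 51% |
| 2% | 0.7 to 1.4 | 51% to 76% |
| 5% | 1.8 to 3.6 | 84% to 97% |
| 10% | 3.6 to 7.2 | 97% to over 99% |

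The 36 to 72 is probably high. The 10-20% refers to relapse that requires restarting an antidepressant, which presupposes having reduced or stopped, and many control patients are not expected to stop.

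**The case against.** A reader might infer that the protocol takes psychiatric admissions out of SAE reporting altogether. The documents do not support that. The sentence does contain a condition about worsening, and the sensible reading attaches it to the pre-existing condition. Screening removes patients with a PHQ-9 of 12 or more, a GAD-7 of 10 or more, any suicidal ideas or current psychiatric treatment for depression, so a relapse severe enough for admission is a plain change from the entry state. The expected-event list is applied to SAEs. Events that are fatal, life-threatening, disabling or otherwise medically important can be serious without relying on the hospitalisation criterion.

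Nor would an event graded as an AE vanish. Relapse still has to be reported, and any reported adverse event goes to the Programme Manager as quickly as possible and then to the Chief Investigator or a PI. PHQ-9, GAD-7 and suicidal ideas are collected at every follow-up. The Causality section describes PIs at each University, which suggests a small group of graders and not 134 practices each deciding alone.

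A reader might also infer that these admissions would make up most of the SAEs that matter. With no admission rate in the documents, that cannot be shown.

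All of this stands and limits the point to ambiguous wording. It does not remove the point, because the intended reading has to be inferred, the alternative routes are discretionary, and none of them places an admission graded as an AE in a planned safety output.

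**Conclusion.** The exclusion sentence is ambiguous on an event central to this trial's safety claim, and Definitions, Causality and section 6.4.1 need to be reconciled. A site that follows the literal text could grade an admission for relapse as an AE. That event would then not be subject to the 24-hour report, would reach the IDMC only at the discretion of the Chief Investigator or a PI, and would be absent from the SAP 4.7 listing.

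The number of events affected is probably small and cannot be derived from the documents; the range in the working rests on assumed admission rates. In a listing of individual events, even one or two omissions matter. No sample size, endpoint or efficacy analysis is affected. The conclusion assumes that no site guidance outside these documents already fixes the reading.

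**What to change.** Two changes to the protocol:

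1. In Definitions, move the qualifier to the condition, for example: hospitalisation for a pre-existing condition that has not worsened since baseline, including a planned elective procedure for it, is not an SAE.
2. In section 6.4.1, add that a listed event meeting any seriousness criterion in Definitions is reported as an SAE, classed as related and expected where that applies, and not only as an AE.

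SAP 4.7 can then stay as it is, since its listing would contain these events. It is not necessary to declare every admission for named psychiatric reasons an SAE. That goes beyond removing the ambiguity, and the grading of individual cases remains with the PI or delegate.

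The cost is a short amendment, a note to sites and a few more SAE forms. If the sponsor already intends this reading, the amendment only writes it down.

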## Causality

A complete assessment of the causality must always be assessed by a medically qualified doctor who is registered on the delegation of responsibility log; this will usually be the Principal Investigator at each University (below).

| Relationship      | Description                                                                                                                                                                                                                                                                                                        | Event Status                                            |
|-------------------|--------------------------------------------------------------------------------------------------------------------------------------------------------------------------------------------------------------------------------------------------------------------------------------------------------------------|---------------------------------------------------------|
| Unrelated  | There is no evidence of any causal relationship                                                                                                                                                                                                                                                                    | Not related to treatment                                |
| Unlikely   | There is little evidence to suggest there is a causal relationship (e.g. the event did not occur within a reasonable time after administration of the study treatment). There is another reasonable explanation for the event (e.g. the participant’s clinical condition, other concomitant treatment).            | Not related to treatment                                |
| Possibly   | There is some evidence to suggest a causal relationship (e.g. because the event occurs within a reasonable time after administration of the study treatment). However, the influence of other factors may have contributed to the event (e.g. the participant’s clinical condition, other concomitant treatments). | Related and expected SAE/
Related and unexpected SAE |
| Probably   | There is evidence to suggest a causal relationship and the influence of other factors is unlikely.                                                                                                                                                                                                                 | Related and expected SAE/
Related and unexpected SAE |
| Definitely | There is clear evidence to suggest a causal relationship and other possible contributing factors can be ruled out.                                                                                                                                                                                                 | Related and expected SAE/
Related and unexpected SAE |

In terms of event status; **Not related to treatment** would highlight that the SAE is not related to the trial treatment. **Related and expected** SAE would signify that the SAE is related to the trial treatment and is expected (according to the list of expected events listed in the protocol). **Related and unexpected** SAE would be classified as an SAE which is related to the trial treatment and is unexpected in terms of the events listed in the protocol.

In the case of discrepant views on causality between the Investigator and others, the SCTU will classify the event as per the worst case classification I and where applicable the Ethics Committee will be informed of both opinions within the required timelines.

## Expectedness

Expectedness assessments are made against the list of expected events below:

### 6.4.1 Expected Adverse Events:

|                                           |                                                                                                                                                                                                           |
|-------------------------------------------|-----------------------------------------------------------------------------------------------------------------------------------------------------------------------------------------------------------|
| Mild antidepressant withdrawal symptoms   | Likely to occur in around half of patients reducing and stopping their antidepressants. If mild enough to be tolerated by patient, and short-lived (up to two weeks), these do not need reporting as AEs. |
| Moderate to severe withdrawal symptoms    | If severe or prolonged withdrawal symptoms occur, requiring restarting of antidepressant, please report as related and expected AE.                                                                       |
| Relapse of depression or anxiety disorder | May occur in 10-20% of patients over the one year follow-up, requiring restarting of antidepressant. Please report as related and expected AE.                                                            |

The nature or severity of should be considered when making the assessment of expectedness. If these factors are not consistent with the current information available then the AE should be recorded as 'unexpected'.

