## Control arm

In the control arm, participating practices will be informed that the recruited patients are potentially eligible for tapering off antidepressants. Their electronic medical records will be flagged and patients will be asked to make an appointment either remotely or in person as part of usual care to see their GPs/NPs for a review, but they will not be trained in best practice in tapering, unlike practitioners in the intervention arm.

Alerting the control arm practices to the potential eligibility of patients for tapering off antidepressants, will result in some patients tapering and ceasing treatment. Some patients would have discontinued treatment anyway, as part of usual care. This will be permitted within the trial. Our power calculation for the secondary outcome of antidepressant discontinuation in the main trial assumes a 7% discontinuation rate in the control practices, which is the rate found in previous studies of simply prompting GPs to review patients potentially eligible for discontinuation (Johnson et al, 2012, Eveleigh 2015).

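### Section 6.4.1 labels relapse and severe withdrawal as related in advance, in both arms, and gives no matching row to moderate-to-severe withdrawal endured without a restart

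*Combined protocol and SAP*

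**What the plan says.** The protocol's Expectedness section introduces the list in 6.4.1: "Expectedness assessments are made against the list of expected events below". The list has three rows.

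- Mild withdrawal: "If mild enough to be tolerated by patient, and short-lived (up to two weeks), these do not need reporting as AEs".
- Withdrawal headed as moderate to severe: "If severe or prolonged withdrawal symptoms occur, requiring restarting of antidepressant, please report as related and expected AE".
- Relapse of depression or anxiety: "May occur in 10-20% of patients over the one year follow-up, requiring restarting of antidepressant. Please report as related and expected AE".

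A closing note adds that nature and severity must be weighed, and that an event out of line with current information is to be recorded as unexpected.

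Other sections bear on the same events.

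- Definitions makes an adverse event "any untoward medical occurrence in a participant or clinical study participant which does not necessarily have a causal relationship with study treatment or participation", whatever the causality judgement.
- Causality: "A complete assessment of the causality must always be assessed by a medically qualified doctor".
- Serious Adverse Events: "The Chief Investigator will assign the causality and expectedness of the event". Safety of Participants repeats this, and routes any adverse event reported by a patient or practitioner to the Programme Manager.
- Consent Procedure leaves tapering in the control arm to the patient and the prescriber.
- SAP 4.7 plans a listing of serious events, related and unrelated, with a summary table if needed.

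**The concern.** Relapse and withdrawal are the harms most to be expected from a programme that helps people stop antidepressants. Two features of 6.4.1 affect how they are classified.

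First, the label 'related' is built into the reporting instruction. It does not depend on arm, on whether the patient reduced the drug, or on a doctor's view of the case.

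Second, the withdrawal instruction is tied to a restart. Only a patient who has stopped can restart, and stopping is what the intervention is meant to change. How an event is coded can therefore depend on something that differs between arms by design.

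At stake are the relatedness shown in the final listing of serious events, if the preset label is carried over to an event that turns serious, and the safety information that reaches the ethics committee and the data monitoring committee. The trial's other measures fill the gap only in part. PHQ-9 and GAD-7 are collected every three months in both arms, but relapse as such is not an endpoint. The withdrawal scale (DESS) is not collected at 9 or 12 months, so withdrawal from later tapering depends on adverse-event reporting.

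**Working it through.** The plan states no figure on this point, so the check sets the sections side by side and applies them to typical records.

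**Step 1: relatedness.** 6.4.1 fixes it as related in both reportable rows. Causality requires a doctor's assessment always. Both instructions cannot be followed unless the assessment always happens to return 'related'.

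**Step 2: typical records.**

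| Record | Mild row | Withdrawal row | Relapse row | Result |
|---|---|---|---|---|
| Severe withdrawal, drug restarted | No | Yes | No | Related and expected, without assessment |
| Severe or month-long withdrawal, no restart | No: beyond the exemption | No: restart condition not met | No | An adverse event by definition; no row, coding unclear |
| Moderate withdrawal lasting one week, no restart | No: not mild | Heading fits, instruction does not | No | Same |
| Relapse in a control patient who never tapered | No | No | Yes by name; the instruction to report stands alone | Related and expected, although no drug was reduced |

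The second and third records show the gap between the exemption and the reporting row. A patient still tapering is in the same position, having nothing yet to restart. The fourth shows the preset label giving an answer that a case assessment need not give.

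**Step 3: where the label could travel.** SAP 4.7 lists serious events by relatedness. The protocol judges the expectedness of serious events against this same list. Safety of Participants sends related and unexpected serious events to the ethics committee within 7 days if fatal or life-threatening and otherwise within 15. Serious events also go to the data monitoring committee. The preset label is written for adverse events in general, so carrying it over to a serious one is a risk and not a stated rule.

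**Step 4: whether a size can be given.** It cannot. The documents give no relapse rate for patients who stay on treatment and no expected discontinuation rate for the intervention arm. The control figure, from a power calculation that "assumes a 7% discontinuation rate in the control practices", uses a different definition: Discontinuation of Antidepressants requires two months off the drug, and expects those who resume to do so within a month. It therefore misses many early restarters and cannot serve as the share of controls able to restart.

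**The case against.** A reader might infer that the plan counts these harms only when the drug is restarted, so that equal relapse would appear as an excess in the intervention arm. The documents do not support that.

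- 6.4.1 never says 'only'. It is a list for judging expectedness, and Definitions and Safety of Participants keep every other relapse or withdrawal episode as an adverse event.
- In the relapse row the mention of restarting is descriptive, and the instruction to report is a separate sentence without a condition.
- Multiplying the 10-20% relapse figure by the 7% control discontinuation rate would not measure under-counting. The first is already described as relapse needing a restart, and the second excludes early restarters.
- The SAP plans no comparison of adverse-event counts between arms.

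A reader might also infer that the label removes grave events from expedited reporting. That too goes further than the text. For serious events the Chief Investigator assigns causality and expectedness, and the closing note in 6.4.1 lets a severe event be recorded as unexpected.

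The narrower defence is that the conflict concerns the Causality section alone, whose related categories carry only serious-event statuses. This has some force: the Chief Investigator's role for serious events does not itself contradict a default for non-serious ones. But the sentence on medical assessment has no such limit. Even if it had, a default of 'related' for a control patient on unchanged medication would still have no stated basis.

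**Conclusion.** The point holds as a defect of classification and clarity. 6.4.1 presets relatedness in both arms against the Causality section, and moderate, severe or prolonged withdrawal without a restart has no row that fits. These events remain adverse events, but reporters and assessors have no clear instruction for them, and the coding turns on having stopped.

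Its reach is limited. The non-inferiority analysis of PHQ-9 at 6 months and the sample size are unaffected, and no planned between-arm analysis is biased. What could be wrong is the relatedness shown in the listing of serious events and the information reaching oversight, on the assumption that the preset label is carried over to serious events. The number of events affected is not estimable from the documents. The correction is still worth making, because these are the trial's principal harms and it is cheap.

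**What to change.** Reconcile Definitions, Causality, 6.4.1 and Safety of Participants. The changes concern reporting only and leave patient care as it is.

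1. In both reportable rows, replace the instruction to report as related and expected with one to report as an adverse event, with causality assessed per event under the Causality section, in both arms.
2. Define the reportable withdrawal event as anything beyond the existing exemption for mild symptoms of up to two weeks. Define relapse as any relapse of depression or anxiety. Neither should depend on whether the antidepressant was stopped or restarted. Record restart as a separate field.
3. Keep the closing note on nature and severity, so that expectedness is still judged per event. The wider definitions should not themselves make these events expected.

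The cost is two table rows, one field on the adverse-event form and somewhat more reports.
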